## Abstract

**Background:**

Considering the extreme shortage of smoking cessation services in China, and the acceptability, feasibility and efficacy of mobile phone-based text message interventions for quitting smoking in other countries, here we propose a study of “the efficacy of mobile phone-based text message interventions (‘Happy Quit’) for smoking cessation in China”. The primary objective of this proposed project is to assess whether a program of widely accessed mobile phone-based text message interventions (‘Happy Quit’) will be effective at helping people in China who smoke, to quit. Based on the efficacy of previous studies in smoking cessation, we hypothesize that ‘Happy Quit’ will be an effective, feasible and affordable smoking cessation program in China.

**Methods/Design:**

In this single-blind, randomized trial, undertaken in China, about 2000 smokers willing to make a quit attempt will be randomly allocated, using an independent telephone randomization system that includes a minimization algorithm balancing for sex (male, female), age (19–34 or >34 years), educational level (≤ or >12 years), and Fagerstrom score for nicotine addiction (≤5, >5), to ‘Happy Quit’, comprising motivational messages and behavioral-change support, or to a control group that receives text messages unrelated to quitting. Messages will be developed to be suitable for Chinese. A pilot study will be conducted before the intervention to modify the library of messages and interventions. The primary outcome will be self-reported continuous smoking abstinence. A secondary outcome will be point prevalence of abstinence. Abstinence will be assessed at six time points (4, 8, 12, 16, 20 and 24 weeks post-intervention). A third outcome will be reductions in number of cigarettes smoked per day.

**Discussion/Implications:**

The results will provide valuable insights into bridging the gap between need and services received for smoking cessation interventions and tobacco use prevention in China. It will also serve as mHealth model for extending the public health significance of other interventions, such as mental health interventions.

**Trial registration:**

NCT02693626 (Registration data April 11, 2016).

## Background

### Tobacco use and cigarette smoking in China

Tobacco use is the leading cause of avoidable morbidity and mortality in China (a country does not have a comprehensive tobacco control policy) [1, 2]. From 1880 to 2009, annual global consumption of cigarettes increased from an estimated 10 billion cigarettes to approximately 5.9 trillion cigarettes, with 38 % of the total consumption in China [3].

According to the Global Adult Tobacco Survey in 14 countries, more than half of men (52.9 % of men and 2.4 % of women) were current tobacco smokers in China [4, 5]. Tobacco smoking was responsible for about 673,000 premature deaths in Chinese adults who were 40 years of age or older in 2005 [1]. Total tobacco-attributable deaths will rise from 5.4 million in 2005 to 6.4 million in 2015 and 8.3 million in 2030 [6], while China’s annual tobacco-attributable deaths could rise to 2 million by the year 2025 [7]. On the basis of current consumption patterns, approximately 450 million adults will be killed by cigarette smoking between 2000 and 2050 [8]. These epidemiological studies demonstrate the serious nature of tobacco use in China and also highlight the need for smoking cessation interventions.

### Shortage of smoking cessation services in China

Smoking cessation rates are very low. Insufficient smoking cessation services are one of the most important contributing factors to the low cessation rates reported in China. Furthermore, clinical studies on smoking cessation remain inadequate in China [7]. A sample from 21 cities in China reported that almost half of smokers intended to quit, however, the prevalence of smoking cessation among those urban-based smokers was only 10.1 % [9].

Quitting rates were also low among Chinese physicians, and China’s medical community has not been sufficiently active in tobacco control [10]. The delivery of advice on quitting smoking was not common among health care providers. For example, a survey revealed that approximately 60 % of smokers were not asked about their smoking behaviours on their visit to a clinician, and approximately 67 % of them were not advised to quit smoking [11]. A survey showed that although the majority of nurses asked about smoking status, few assisted patients with quitting [12].

In order to minimize the huge gap between the need and demand for smoking cessation service, health-care professionals should shoulder leadership to provide smoking cessation services that are readily available, effective and cheap.

### Smoking cessation support delivered via mobile phone text messaging

The rapid development of mobile health technology (mHealth) provides unprecedented opportunities to improve health services and to reach underserved populations. Mobile phone based short text messaging service (SMS) has the potential to deliver smoking cessation support to large population groups, and the effectiveness of SMS programs to improve smoking cessation [13], which has been reported in other countries with different populations [14–18]. Because mHealth may be involved in how well and how quickly mobile phones are integrated into health care, and how well they serve the needs of the entire population, it deserves the attention of both the healthcare and public health community [19].

There are several potential benefits of SMS programs for smoking cessation: a) the easiness of use anywhere at any time; b) cost-effective delivery; c) scalability to large populations regardless of location; d) the ability to tailor messages to key user characteristics (such as age, sex, education); e) the ability to send time-sensitive messages with an ‘always on’ device; and f) the provision of content that can distract the user from cravings. The use of mobile phones for smoking cessation should be encouraged as they become even more ubiquitous and as technological advances increase the number of applications and functions available. Therefore, it is important to design mobile phone-based services that can be effective at helping people who smoke, to quit [14].

Importantly, mobile phone technologies are a way to reach a large proportion of the Chinese population. The number of mobile phone subscribers in China from February 2014 to February 2015 was about 1.29 billion (http://www.statista.com/). More than 90 % of Chinese use mobile phones; thus, it is a widely accessible technology that is highly suited to interventional purposes in China. Furthermore, the reading and sending of SMS messages are the most frequent activities when Chinese use a mobile phone. There is an urgent need to design such a population-based widely accessible smoking cessation program in China.

### Implications of our experiment

Tobacco use is a major cause of disease burden and the number one preventable cause of death in the world. About one-third of the world’s tobacco is produced and consumed in China. Among the general population of smokers, most report a desire to quit. Unfortunately, the availability of smoking cessation programs in China is extremely limited, and the majority of cessation attempts end in relapse. The rapid development of mobile health technology (mHealth) provides unprecedented opportunities to improve health services and to reach underserved populations, and the effectiveness of text message mobile phone programs to improve smoking cessation has been reported in other countries.

Considering the extreme shortage of smoking cessation programs in China, and the efficacy of mobile phone text message-based program for smoking cessation reported in other countries, we propose to design such a population-based widely accessible smoking cessation program in China. This proposed study is designed to determine the effectiveness of mobile phone-based text message interventions (‘Happy Quit’) for smoking cessation in China, which will be assessed by self-reported smoking abstinence at 4, 8, 12, 16, 20 and 24 weeks post-intervention. This proposed study has important implications in providing valuable insights into bridging the gap between need and services received for smoking cessation interventions and tobacco use prevention in China. It will also serve as a mHealth model for extending the public health significance of interventions, such as mental health interventions.

## Research design and methods

### Hypotheses and theoretical model

Primary Hypothesis: We hypothesize that ‘Happy Quit’ will be tested as an effective, feasible and affordable smoking cessation program in China. To be specific, the text messages intervention group will have higher rates of self-reported continuous smoking abstinence and point prevalence of abstinence when compared to control-group; and by assessing the number of cigarettes smoked per day, the text-based intervention will help those relapse smokers smoke fewer cigarettes than before. Secondary Hypothesis: Mobile phone-based text message interventions (‘Happy Quit’ program) for smoking cessation will have wider influence on smoking cessation in China.

Theoretical model: Fig. 1 illustrates the theoretical model. In this model, text messaging could be applied in healthcare widely: settings range from primary care to community care services to public health; purposes from behavior modification to disease management, treatment and medication adherence to data collection; populations vary from children and adolescents to elderly, from cigarette smokers to Patients with mental illness and other diseases. Figure 2 Shows the worksheet for short message service (SMS) implementation planning for ‘Happy Quit’ program.

**Fig. 1 Fig1:**
[figure not shown]
Text messaging in healthcare

**Fig. 2 Fig2:**
[figure not shown]
Worksheet for short message service (SMS) implementation planning

## Methods

### Setting and sample

This large, simple randomized trial of a new smoking cessation service will be conducted using mobile phone text messaging in China. A total of 2000 eligible participants will be selected randomly to the intervention or control groups.

Eligibility: daily smokers 18 years of age and older living in China.

Inclusion Criteria:Daily Chinese cigarette smokers.18 years of age and older living.Being able to read and write in Chinese.Owning a text-capable cell phone and knowing how to text.Willing to make an attempt to quit smoking in the next month.Willing to provide informed consent to participate in the study.

Exclusion Criteria:NonsmokersBelow 18 years old.Unable to read and write in Chinese.

No restrictions will be placed on location within mainland China. Given that this study will be mainly performed with text messaging, no restrictions will be placed on setting or location for confirmation of informed consent or for data collection.

### Procedures

We will advertise this service to smokers on the radio, bus billboards and online (e.g., websites, QQ, WeChat) and in newspapers, hospitals and pharmacies. Potential participants will register their interest by sending a text message. Research assistants then will telephone respondents to assess eligibility and collect baseline data.

In this single-blind, randomized trial, undertaken in China, smokers willing to make a quit attempt will be randomly allocated, using an independent telephone randomization system that includes a minimization algorithm balancing for sex (male, female), age (19–34 years, >34 years), educational level (to age ≤12 years, >12 years), and Fagerstrom score for nicotine addiction (≤5, >5), to a mobile phone text messaging smoking cessation program (‘Happy Quit’), comprising motivational messages and behavioral-change support, or to a control group that receives text messages unrelated to quitting. The system will automatically generate intervention or control group texts according to the allocation. Outcome assessors will be masked to treatment allocation.

Participants will be allocated to either a control group or to a group that receives the mobile-based smoking cessation program. All participants will be free to participate in any other smoking cessation service or support that they wish to use if possible and available. All Participants in both the intervention group and control group will be asked to set a quit date within one month of randomization.

Messages will be developed with the input of smokers and smoking cessation professionals. The intervention will include motivational messages and behavior-change techniques. Messages will encourage participants to persevere with the quit attempt and will focus on their success so far. The motivational messages will provide positive feedback and emphasize the benefits achieved by quitting and provide information about the consequences of smoking, how to quit and stay quit, and how others would approve of successful abstinence. The behavior change messages will prompt participants to get rid of cigarettes, ashtrays, and lighters and to avoid environments where they would normally smoke, and encourage participants to identify the challenges of quitting and plan how to overcome them. The messages also promote the use of nicotine replacement therapy if possible and available.

Participants who allocate to the intervention group will receive this program of interventions, which will be based around setting a quit date within 30 days of randomization. As described above, they will receive regular, personalized text messages providing smoking cessation advice, support and distraction. This content will also cover information relevant to quitting—for example, symptoms to expect on quitting, tips to cope with craving, tips to avoid weight gain and improve nutrition; advice on avoiding smoking triggers; instructions on breathing exercises to perform instead of smoking; motivational support (for example feedback on amount of money and life years saved) and distraction (for example, general interest, sports, fashion, trivia, travel). The messages will be developed by a multidisciplinary team including young adults, health related researchers and experts in cognitive behavioral therapy, and smoking cessation. An algorithm based on keyword matching will be developed to match participant characteristics (preferences, smoking history, barriers to cessation, etc.) with a database of over 1000 text messages so that an individualized program will be provided.

A quit day will be negotiated with each participant, and five messages will be sent per day for the time leading up to the quit day and the following 12 weeks. On the quit day, a free month of outgoing text messaging also begins, with participants encouraged to tell all their friends and family they are quitting on that day. This process will encourage communication and support, and also help with distraction, given the time that will spend in writing and receiving text messages. Several other text message based services will also be provided for the intervention group: Quit buddy (participants with similar characteristics and quit days will be put in touch with each other); text crave (participants could ‘pull’ text messages on demand by sending a text message to a short code number and they would receive a tip on how to get through their cravings); and TXT quizzes (questions will be sent out, following by answers the next day).

Twelve weeks after randomization, coinciding approximately with the end of the free text messaging month, the intervention will become much less intensive, with the number of sent text messages reduced from five per day to three per week until the end of the 24 week (that is, six month) follow up. These messages will focus on maintaining cessation among those who had quit. Control group participants only will receive one text message every week, thanking them for being in the study, providing study centre contact details, and reminding them of the time until their free month at the end of follow up.

Anyone who completes follow up (a total of 24 weeks) will be rewarded with a free month of text messaging and 100 CNY mobile phone based payment (whether they quit or not), a reminder of these benefits will be sent to the participants at the beginning of the study and each month. All participants will be checked at 4, 8, 12, 16, 20, 24 week points about continuous smoking abstinence, point prevalence of abstinence, how many cigarettes per day during the last 4 weeks and past 1 week if they are still smoking, levels of craving, weight and so on. Symptoms of anxiety and depression, sleeping quality will be only asked at before quit day, 8 week, and 24 week points, and a phone call will be made for their significant other (e.g., family member, friend) to make a further confirmation about their quit status.

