### Outcome measures

**Self-reported continuous smoking abstinence**: no more than five cigarettes smoked in the past week at 4 weeks follow-up and no more than five cigarettes smoked since the start of the abstinence period at 6 months of follow-up. **Point prevalence of abstinence**: not even a puff of smoke, for the last 7 days, at 4, 8, 12, 16, 20 and 24 weeks. Abstinence will be assessed by means of brief telephone interviews at each time point. **Cigarettes smoked per day:** number of cigarettes smoked per day within the past 4 weeks and the approximately total number of smoked cigarettes within the past 4 weeks.

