### Statistical methods

**Power estimation:** On the basis of the results of the recent review paper [20] and the large sample size study published in the Journal of Lancet [15], we estimated that the control group quit rate would be around 5 % (ranged from 4.9 to 27.6 %) and loss to follow-up will be 10 %, with 95 % as an accepted standard for statistical significance. According to a power analysis, only 486 participants will be required in this group. However, given that none of the study from China, we plan to assess 4000 participants, and 2000 participants (1000 participants in each group) will be eligible and randomize to intervention or control groups. With 10 % loss to follow-up, we will have a 90 % of participants available for analyses, which will provide sufficient power to detect a difference.

**Comparison between Intervention group and control group:** For the data, *t* test, Chi-square test and logistic regression will be used for the comparison of the self-reported continuous smoking abstinence, point prevalence of abstinence, cigarettes smoked per day between the two groups. Repeated measures analyses of variance will be used for the comparison of levels of craving, weight, sleep quality, levels of anxiety and depression between the two groups. An alpha level of 0.05 (two-tailed) will be chosen for all statistical tests in this study. For the primary analysis we will use multiple imputation, which uses the observed predictors of outcome and the predictors of loss to follow-up to impute missing outcome data, thus attempting to correct for any potential bias caused by it (using the intent-to-treat principle, missing will be counted as smoker).

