However, there are some limitations in this proposal: First of all, this proposal will not provide biochemical verification for self-reported claims of abstinence due to the geographic spread of the sample, cost and other practical concerns. However, false reporting is considered to be minimal when there is little or no personal contact between treatment provider and participants (i.e. only through telephone); hence, it not likely that misreporting could compromise conclusions. Furthermore, the biochemical tests are not perfect. Cotinine has an in-vivo half-life of about 20 h, and can only be detected with a cotinine test for a few days after the use of tobacco. Carbon monoxide can be detected only for about 24 h after tobacco use. Secondly, although efforts will be made to ensure that the research staff remain be masked to whether a participant will be in the intervention or control group, occasionally trial participants would reveal this information to the study staff. This information could bias our estimates of self-reported abstinence. Thirdly, participants who will be allocated to the control group could reduce their motivation to quit. In order to address this issue, the control group will be recommended to receive smoking cessation care once the study is over. Despite those limitations, the expected benefits of this research project are numerous, such as providing interactive and individualized mobile phone-based text message smoking cessation program, developing suitable mhealth model in China, promoting mhealth in smoking cessation and other mental disorders’ treatment and prevention.

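### The planned call to a significant other to confirm quit status has no role in the outcomes or analysis, and the assurance about misreporting does not address a difference between arms

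*Protocol article*

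**What the plan says.** All references are to the protocol article.

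- **Collateral call (Procedures).** Someone close to the participant is telephoned "to make a further confirmation about their quit status". The call stands in the same sentence as the anxiety, depression and sleep questions asked before the quit day and at weeks 8 and 24. It therefore appears to belong to weeks 8 and 24, but the wording is not explicit.
- **Outcomes (Outcome measures).** Continuous abstinence is named as self-reported and begins with "no more than five cigarettes smoked in the past week at 4 weeks follow-up"; the six-month part allows the same five cigarettes from the start of the abstinence period. Point prevalence covers the last seven days. Both come from brief telephone interviews. The call to the significant other is not mentioned.
- **Analysis (Statistical methods).** The section names the tests, the imputation and the handling of missing outcomes. It gives the collateral information no role. On the error rate it says: "An alpha level of 0.05 (two-tailed) will be chosen for all statistical tests in this study".
- **Verification (Discussion).** The article discloses that there will be no biochemical check. It argues that false reports are few when provider and participant have little personal contact, and concludes that "it not likely that misreporting could compromise conclusions".
- **Contact and masking (Procedures).** The intervention arm gets five texts a day to 12 weeks and three a week to week 24, plus a quit buddy, on-demand craving texts and quizzes. The control arm gets one text a week. Only outcome assessors are said to be masked.

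**The concern.** The trial plans to collect one independent check on quit status, and the article does not say what the check is for. As the outcomes are worded, a participant who claims abstinence counts as abstinent even if the significant other says otherwise.

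The Discussion's reassurance does not fill this gap. False reporting at the same rate in both arms does not create a difference where there is none. False reporting at different rates does. There is a reason to consider it here: participants supply the outcome, they are not said to be masked, and one arm has months of messages that praise success and stress the approval of others. If that arm over-reports more, the primary comparison is biased towards benefit. A large sample does not help, because it makes a small biased difference easier to detect.

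**Working it through.** **Inputs from Statistical methods.** Two-sided alpha is 0.05. On the control rate: "the control group quit rate would be around 5 % (ranged from 4.9 to 27.6" per cent. On attrition: "loss to follow-up will be 10" per cent. On size: "2000 participants (1000 participants in each group) will be eligible and randomize to intervention or control groups". That is 1000 per arm if missing counts as smoking, or about 900 per arm analysed without the 10% lost.

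**The plan's own figures.** The article gives no misreporting rate, so there is nothing to reproduce on this point. Its one sample-size figure ("only 486 participants will be required in this group") cannot be derived, because no intervention quit rate or power is stated. Nothing below depends on it.

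**Assumptions (not from the documents).** True abstinence *p* is the same in both arms. A fraction *f* of those still smoking falsely claim abstinence.

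**Step 1: reported rate** = p + (1 − p) × f. With p = 5%:
- f = 2%: 0.05 + 0.95 × 0.02 = 6.90%
- f = 3%: 0.05 + 0.95 × 0.03 = 7.85%
- f = 4%: 0.05 + 0.95 × 0.04 = 8.80%

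**Step 2: chance of rejection.** Two-proportion test with pooled null variance. Let d be the difference in reported rates, p̄ their mean, s0 = √(2p̄(1 − p̄)/n) and s1 = √(pC(1 − pC)/n + pI(1 − pI)/n). The chance is Φ((d − 1.96·s0)/s1) plus a small opposite tail.

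Example, 2% against 4% with n = 1000: d = 0.0190, s0 = 0.01203, s1 = 0.01202. Then (0.0190 − 0.02357)/0.01202 = −0.38, and Φ = 0.352.

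| False claims, control vs intervention | Reported rates | 1000 per arm | 900 per arm |
|---|---|---|---|
| 2% vs 2% | 6.90% vs 6.90% | 5.0% | 5.0% |
| 2% vs 3% | 6.90% vs 7.85% | 12.8% | 12.0% |
| 2% vs 4% | 6.90% vs 8.80% | 35.2% | 32.2% |

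The same *f* is applied to all smokers. If those lost count as smokers they cannot make a false claim, so the rate among respondents would have to be slightly higher.

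**Step 3: higher quit rates.** For 2% against 4% and 1000 per arm, the chance is 22.7% at p = 10% and 10.9% at p = 27.6%, the top of the stated range.

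**Step 4: tipping point on self-report alone.** With 900 per arm and 45 reported quitters (5%) in control, 65 in the intervention arm gives p = 0.049 (uncorrected chi-square), while 64 gives p = 0.060. Twenty excess claims are enough: 20/900 = 2.2 points, or 20/855 = 2.3% of the intervention arm's smokers. With no false claims in control and 900 per arm, the excess that gives a 50% chance of a significant result is about 2.3% at p = 5%, 3.3% at p = 10% and 5.8% at p = 27.6%.

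**The case against.** The other side has several good points.

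- **This is a condensed article.** Rules for discordant or unreachable proxies may be in an analysis plan not shown here. A reader might infer that the collateral information will be discarded; the article does not say so. What stands is narrower: it fixes the abstinence outcomes on self-report and assigns the call no part in them.
- **The weakness is disclosed.** Lack of biochemical verification is the first limitation listed, and possible bias from unmasking of staff is conceded. The fault is in the reassurance, not in concealment.
- **There are safeguards.** Assessors are masked, payment does not depend on quitting, texts are system-generated, and both arms set a quit date and are asked at the same six time points. These reduce the motive to over-report in general. They do not make it equal between arms.
- **The contrast in contact is easily overstated.** By week 24 it is three texts a week against one. Participants are also encouraged to announce on the quit day that they are quitting, which is not a claim to have succeeded.
- **The rates are assumed.** A reader might infer that differential misreporting is likely to produce a positive result by itself. The documents do not support that; the arithmetic shows what is possible, not what is probable.
- **Proxies are imperfect.** They may be unreachable or mistaken. They cannot readily verify a five-cigarette allowance, and in the intervention arm they may be the people the programme prompted the participant to tell. This argues for a supportive role only.

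It would also be wrong to say that nothing could bound the bias without proxies: Step 4 does so from self-report alone.

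**Conclusion.** The point holds in a limited form. The protocol plans a collateral check but gives it no role in the outcomes or analysis. Its assurance about misreporting answers a question about level, when the comparison is sensitive to a difference.

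The size depends on assumptions that the documents cannot settle. At 5% true abstinence in both arms and 1000 per arm, one extra percentage point of false claims over a 2% base raises the false-positive chance from 5% to about 13%, and two extra points raise it to about 35%. The effect is smaller at higher quit rates. This does not show that a positive result would be spurious, and it does not call for replacing the primary outcome. It is a change that should be made, because data that bear on the question are already to be collected.

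**What to change.** 1. Keep self-reported continuous abstinence as primary.
2. Name a supportive analysis of collateral-confirmed continuous abstinence at 24 weeks (self-reported abstinent and not contradicted by the significant other), analysed like the primary. Add a variant that counts unconfirmed quitters as smokers.
3. State at which weeks the calls are made, and that they are made in both arms by masked callers.
4. Report discordance and proxy non-response by arm.
5. Add a tipping-point analysis giving the differential misreporting that would remove a significant result.
6. Reword the Discussion statement so that it depends on these results.

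The cost is a few lines of text and a small amount of extra analysis, since the calls are already planned. Confirmed rates will be somewhat lower than self-reported ones, and the limits of proxy reports mean that the result should be read as supportive only.
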